### Primary endpoint

#### Clinical endpoint

1) Difference in average stool frequency during weeks 11–12 of the treatment period.

#### Mechanistic endpoint

1) Difference in mast cell numbers per mm^2^ during weeks 11–12 of the treatment period.

#### Secondary endpoint

Clinical secondary endpoints during weeks 11 and 12 of the treatment period:

1) Average daily severity of abdominal pain on a 0 to 10 scale.

2) Days with urgency.

3) Mean stool consistency using Bristol Stool Form Score.

4) Global satisfaction with control of IBS symptoms as assessed from the answer to the question ‘Have you had satisfactory relief of your IBS symptoms this week? Yes/No.’

Mechanistic secondary endpoints during weeks 11 and 12 of the treatment period:

1) Mast cell tryptase release during 6-hour biopsy incubation

2) IL-1β, TNF-α, histamine and serotonin secretion during same incubation

3) Small bowel tone assessed by volume of fasting small bowel water

4) Fecal tryptase activity

5) Difference in primary outcome measure between those with different TNFSF15 polymorphism

Ancillary secondary endpoints during weeks 11 and 12 of the treatment period:

1) EuroQol-5D (EQ-5D)

2) Centers for Disease Control and Prevention Health-Related Quality of Life (CDC HRQOL4)

3) Hospital, Anxiety and Depression Scale (HADS)

4) Patient Health Questionnaire-15 (PHQ-15)

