**Methods/design:**

This is a multicentre randomised, double-blind, placebo-controlled trial using a parallel group design. At least 108 participants with diarrhoea-predominant IBS will be recruited through at least six hospitals. The intervention is a 12-week course of 2g mesalazine granules taken up to twice a day. The comparator is a blinded placebo granule formulation.

Outcome measures include stool diaries, symptom questionnaires, stool and blood samples together with rectal mucosal biopsies. The daily stool diary will record stool frequency and form, urgency, bloating, abdominal pain and a global satisfaction with control of IBS scored each week. The questionnaires will assess bowel symptoms, while the samples and biopsies will be used to analyse underlying mechanisms of any response.

Primary outcome will be the average stool frequency during weeks 11 and 12 of the treatment period and will be compared between treatment arms using an analysis of covariance in the form of a general linear model incorporating baseline characteristics that are thought *a priori* to strongly predict outcome. The primary efficacy parameter will be the difference in mean frequency between treatment arms.

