### Trial objectives

The trial objectives were as follows:

1) To assess the effect of mesalazine on stool frequency.

2) To assess the effect of mesalazine on

·• Overall IBS symptoms

·• Mast cell numbers, mucosal lymphocytes and faecal tryptase activity

·• Release of mast cell mediators from rectal biopsies.

·• Small bowel tone by measurement of fasting small bowel water content using magnetic resonance imaging (MRI).

·•To assess ability of biomarkers (mucosal/MRI parameters) to predict treatment response

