#### Blood sample

Serum isolated from blood samples were analysed for inflammation biomarkers. DNA isolated from blood samples were analysed for any genetic link between polymorphisms and treatment response.

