### Statistical analysis

The primary analysis will be performed on the full analysis set (that is, all randomised participants for whom the primary endpoint (symptoms at 11 and 12 weeks) is available) using an analysis of covariance in the form of a general linear model incorporating terms for baseline frequency, treatment arm, centre, and other baseline characteristics which are thought a priori to strongly predict outcome.

Secondary and mechanistic endpoints were treated similarly, after transformation to approximate normality as required for continuous variables, while binary and count outcomes were handled by logistic or Poisson regression, as appropriate. All analyses were performed using the current version of STATA (StataCorp, Texas, USA), adopting the intention to treat principle following multiple imputation for missing data (with a sensitivity analysis for the missing at random assumption for the primary outcome). For mechanistic variables a per-protocol analysis was additionally performed.

No interim or subgroup analyses were planned for efficacy.

Assessment of safety followed the same principles as the assessment of efficacy except that the safety set (that is, all randomised participants who receive at least one dose of the study drug) were used.

Procedures for missing, unused and spurious data were handled by multiple imputation using the method of chained equations.

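### The TNFSF15 endpoint, as worded, compares stool frequency between genotypes and so does not test treatment response; read as an effect by genotype, it conflicts with the no-subgroup statement

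*Protocol article*

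**What the plan says.** Four places in the protocol article bear on this point.

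- *Secondary endpoint*, mechanistic item 5: "Difference in primary outcome measure between those with different TNFSF15 polymorphism". Treatment arm is not mentioned.
- *Abstract, Methods/design* separates the patient-level outcome from the treatment effect. The outcome: "Primary outcome will be the average stool frequency during weeks 11 and 12 of the treatment period". The effect: "The primary efficacy parameter will be the difference in mean frequency between treatment arms".
- *Blood sample* states what the genetic work is for: "DNA isolated from blood samples were analysed for any genetic link between polymorphisms and treatment response".
- *Statistical analysis* gives the primary model as a "general linear model incorporating terms for baseline frequency, treatment arm, centre, and other baseline characteristics which are thought a priori to strongly predict outcome", adds that "Secondary and mechanistic endpoints were treated similarly", and states "No interim or subgroup analyses were planned for efficacy". It names no interaction term.

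**The concern.** The purpose and the endpoint are different questions. Whether genotype is linked to treatment response is a question about how the mesalazine-placebo difference varies with genotype. Whether stool frequency at the end of treatment differs between genotypes is a question about prognosis, averaged over the two arms. A variant that raises frequency equally under mesalazine and placebo would be a positive finding for item 5 and would say nothing about who benefits from the drug.

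An analyst who follows item 5 literally could report a prognostic variant under the heading of treatment response, or miss a real difference in response. An analyst who follows the *Blood sample* sentence would compare efficacy across genotypes, which the plan says was not planned. A reader of the results could then not tell whether that comparison was prespecified.

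**Working it through.** **1. The sections side by side.**

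| Reading of item 5 | Meets the purpose in *Blood sample*? | Consistent with the no-subgroup statement? |
|---|---|---|
| Literal: stool frequency compared between genotypes | No, it is prognostic | Yes, it is not an efficacy subgroup analysis |
| Loose: between-arm difference compared across genotypes | Yes | No |

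Neither reading satisfies both columns.

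**2. How the literal contrast misleads.** The means below are assumed, in stools/day, with 1:1 allocation within genotype. Take them as means at a given baseline frequency, because the model adjusts for baseline.

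| Case | Non-carriers: placebo, mesalazine | Carriers: placebo, mesalazine | Genotype difference (item 5) | Treatment effects (non-carriers, carriers) | Interaction |
|---|---|---|---|---|---|
| A | 3.1, 1.7 | 4.1, 2.7 | 3.4 − 2.4 = 1.0 | −1.4, −1.4 | 0 |
| B | 3.1, 2.4 | 3.8, 1.7 | 2.75 − 2.75 = 0 | −0.7, −2.1 | −1.4 |

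Item 5 flags case A, where response is the same, and misses case B, where response differs by as much as the whole effect assumed for the trial. A term for treatment arm does not help: without an interaction term the genotype coefficient is still an average over arms.

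**3. Precision of the two contrasts.** The article states no figure for this endpoint, so there is none to reproduce. From *Sample size*, taken as given: 108 completers, 1:1, SD 2.0, effect 1.4/day. Assumed: two genotype groups, the carrier share, and a two-sided 5% level.

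- Genotype main effect: SE = SD × √(1/n₁ + 1/n₀).
- Interaction: each within-genotype treatment effect has variance SD² × (2/n + 2/n) = 4·SD²/n, so SE = SD × √(4/n₁ + 4/n₀), exactly twice the main-effect SE.

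| Carrier share | n₁, n₀ | Main-effect SE | Interaction SE | Interaction 95% half-width (1.96 × SE) |
|---|---|---|---|---|
| 50% | 54, 54 | 2√(2/54) = 0.385 | 2√(8/54) = 0.770 | 1.51 |
| 25% | 27, 81 | 2√(1/27 + 1/81) = 0.444 | 2√(4/27 + 4/81) = 0.889 | 1.74 |

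Power to detect an interaction of 1.4/day is Φ(1.4/SE − 1.96). At a 50% share this is Φ(1.4/0.770 − 1.96) = 44%. It falls to 39% at 30%, 31% at 20% and 19% at 10%. At a 50% share the interaction detectable with 80% power is (1.96 + 0.84) × 0.770 = 2.16/day, more than the whole assumed treatment effect.

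**The case against.** The strongest reply is that the endpoint list is shorthand. Other items in it do not mention arms either, yet are plainly compared by arm, and the section *Primary endpoint* itself speaks of a difference in stool frequency without naming arms. With the purpose given in *Blood sample*, item 5 could fairly be read as the between-arm difference compared across genotypes. This stands as a possible reading, although the abstract's separation of outcome from efficacy parameter favours the literal one. It does not settle the matter, because that reading brings in the conflict with the no-subgroup statement.

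It could also be said that an interaction test is not a subgroup analysis, or that a mechanistic endpoint is not efficacy. But the outcome is the primary efficacy measure and the comparison is of treatment effect across patient groups. If the plan means to exempt it, it should say so.

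It is fair, too, that the factor of two is algebra for any 1:1 trial and measures no error in a stated figure. It shows what the corrected endpoint costs. The SD of 2.0 is unadjusted; baseline adjustment would be expected to shrink both standard errors alike and leave the ratio unchanged.

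Three stronger inferences are not supported:

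- *That item 5 flatly contradicts the no-subgroup statement.* The conflict arises only under the treatment-effect reading.
- *That the biomarker objective is also wrongly analysed.* *Trial objectives* states it as "To assess ability of biomarkers (mucosal/MRI parameters) to predict treatment response", which does not cover a blood genotype. The article gives no analysis for it, and such detail may properly sit in the full protocol or analysis plan, which are not shown.
- *That the trial intends to select patients for mesalazine by genotype.* No section proposes this.

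**Conclusion.** The point holds in this form: item 5 as worded is a prognostic contrast that does not answer the stated genetic purpose, and the reading that would answer it is excluded by the no-subgroup statement. *Secondary endpoint*, *Blood sample* and *Statistical analysis* cannot all be met as they stand. This conclusion rests on the text alone.

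The size of the consequence depends on assumed carrier shares. The contrast that answers the question has twice the standard error of the one written, and at 108 completers its 95% interval would reach at least 1.5 stools/day either side at a carrier share of 50% or below. It can therefore be exploratory only. The matter is confined to one mechanistic secondary endpoint. It should be corrected, but it does not threaten the trial's main conclusion.

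**What to change.** 1. Reword mechanistic item 5 as: *Difference in the treatment effect on average stool frequency (weeks 11–12) between TNFSF15 genotypes.*
2. Estimate it by adding genotype and treatment-by-genotype terms to the primary analysis of covariance. Report the interaction with its confidence interval and label it exploratory.
3. Amend the sentence in *Statistical analysis* to say that no efficacy subgroup analyses are planned other than this exploratory interaction.

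The cost is two changes of wording and two model terms (more if more than two genotype groups are compared), made before the treatment code is broken. Recruitment and the primary analysis do not change. The downside is a wider interval and low power, which the report should state so that a null interaction is not taken as evidence of equal response.

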### Outcome measures

#### Daily symptom and stool diary

Participants completed a daily symptom and stool diary throughout their participation indicating hours of pain, severity of abdominal pain on a 0 to 10 scale, presence of urgency (yes/no) and bloating on a 0–10 scale. They were also asked on a weekly basis the following yes/no question: ‘Have you had satisfactory relief of your IBS symptoms this week?’

#### IBS-D sub-groups

The Rome III criteria questionnaire will be used to assess whether the participant has IBS-D. In addition the participants will answer supplementary questions to identify any cases that are post-infectious IBS-D.

#### Psychological profiles

We used the HADS and PHQ-15 questionnaires, collected at baseline and 12 weeks.

#### Quality of life questionnaires

Quality of Life was assessed using the two generic quality of life measures that had been validated in IBS patient groups: the CDC HRQOL4 [24] and the EQ-5D [25], which has been shown to be sensitive to a successful treatment of symptoms [26].

#### MRI (Nottingham only)

Fasting small bowel water content was assessed using our previously validated MRI technique [27]. The volume of small bowel water gives an indirect assessment of intestinal tone. We have previously shown that small bowel water content is significantly reduced in IBS-D, both fasting and postprandial [28].

#### Flexible Sigmoidoscopy and biopsies (Nottingham only

Patients will undergo an unsedated flexible sigmoidoscopy with biopsy of the sigmoid colon. Biopsies will be taken to investigate mast cells, mRNA for IL-1, TNF-α and protein levels, as well as for tryptase, serotonin and histamine release on incubation of mucosal biopsies.

#### Stool sample

Stool samples will be analysed for proteases and other inflammation biomarkers. Bacterial DNA isolated from stool samples will also be analysed using the HITChip [29].

#### Blood sample

Serum isolated from blood samples were analysed for inflammation biomarkers. DNA isolated from blood samples were analysed for any genetic link between polymorphisms and treatment response.

### Sample size

Our previous study on diarrhoea-predominant IBS patients gives a mean stool frequency of 3.1 (standard deviation 2.0). Tuteja and colleagues reported mesalazine decreasing stool frequency by 1.4 bowel movements per day [14]. We calculated from these data that 108 completed patients (randomized 1:1 to mesalazine or placebo) would give the study an 80% power to detect such an effect at the 1% significance level (90% at 5% significance). As we had not accounted for attrition if participants withdrew, these participants were replaced in order to ensure 108 completed participants.

Much smaller numbers would be needed to assess the effect of mesalazine on mast cell numbers and tryptase release. Corinaldesi *et al*. reported a 36% decrease in mast cell numbers from mean 9.2 (standard deviation 2.5) [13], which would have required just 12 patients to show such a decrease with a power of 90% at the 1% significance level.

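### The stated power for 108 completers (80% at 1%, 90% at 5%) does not follow from the stated difference and SD, which give about 84% and 95%

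*Protocol article*

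**What the plan says.** All the inputs are in the Sample size section of the protocol article.

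- **Variability:** an earlier study by the same group in diarrhoea-predominant IBS "gives a mean stool frequency of 3.1 (standard deviation 2.0".
- **Effect:** a cited small randomised trial "reported mesalazine decreasing stool frequency by 1.4 bowel movements per day".
- **Size and allocation:** "108 completed patients (randomized 1:1 to mesalazine or placebo".
- **Power claimed, said to be calculated from these data:** the design "would give the study an 80% power to detect such an effect at the 1% significance level (90% at 5% significance".
- **Attrition:** "As we had not accounted for attrition if participants withdrew, these participants were replaced in order to ensure 108 completed participants".

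The Abstract gives the target as a minimum: "At least 108 participants with diarrhoea-predominant IBS will be recruited". The Statistical analysis section specifies a covariance-adjusted linear model for the primary outcome. It gives no significance level, and sidedness is not stated anywhere in the article.

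**The concern.** A power statement should be reproducible from the inputs printed beside it. Here the difference, SD, number per arm and two significance levels are all given, yet neither power figure comes out. The two figures also cannot come from a single design, because fixing power at one level largely fixes it at the other.

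This sentence is the only stated basis for the recruitment target. A reader who cannot reproduce it cannot tell whether the difference, the SD, the test or the power is misreported. Nor can they tell how much margin the trial has if the true effect is smaller than 1.4.

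**Working it through.** **Inputs** (Sample size section): difference Δ = 1.4, SD σ = 2.0, n = 108/2 = 54 per arm. The standardised difference is d = 1.4/2.0 = 0.70. A two-sided test is assumed, and a one-sided test is also tried.

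**Step 1. Attempt to reproduce the stated 80% and 90%.** The signal under the alternative is

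λ = Δ / (σ√(2/n)) = 1.4 / (2.0 × √(2/54)) = 3.637.

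By the normal approximation, power = Φ(λ − z), where z is the critical value:

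- two-sided 1%: Φ(3.637 − 2.576) = Φ(1.061) = 85.6%
- two-sided 5%: Φ(3.637 − 1.960) = Φ(1.677) = 95.3%

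The table adds the noncentral t distribution with 106 degrees of freedom.

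| Test, 54 per arm | Power at 1% | Power at 5% |
|---|---|---|
| Stated in the article | 80% | 90% |
| Two-sided, t | 84.2% | 95.0% |
| Two-sided, normal | 85.6% | 95.3% |
| One-sided, t | 89.7% | 97.6% |
| One-sided, normal | 90.5% | 97.7% |

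No row gives either stated figure. One-sided testing widens the gap.

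**Step 2. Completers needed for the stated targets, two-sided.** N = 4(z₁₋α/₂ + z_power)² / d²:

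- 80% at 1%: 4 × (2.576 + 0.842)² / 0.49 = 95.3, so 96 in two equal arms (100 by t)
- 90% at 5%: 4 × (1.960 + 1.282)² / 0.49 = 85.8, so 86 in two equal arms (88 by t)

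Neither target leads to 108. By the normal approximation, 108 is the size for 95% power at two-sided 5%.

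**Step 3. Are the two stated figures compatible with each other?** This check does not depend on Δ, σ or n.

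- 80% at two-sided 1% needs λ = 2.576 + 0.842 = 3.417. Power at 5% is then Φ(3.417 − 1.960) = Φ(1.457) = 92.7%, about 93%.
- 90% at two-sided 5% needs λ = 1.960 + 1.282 = 3.242. Power at 1% is then Φ(3.242 − 2.576) = Φ(0.666) = 74.7% (about 74% by t).

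Back-solving by t at SD 2.0 and 54 per arm, 80% at 1% needs a difference of about 1.34, while 90% at 5% needs about 1.26. One undisclosed difference cannot produce both.

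**Step 4. Can rounding explain it?** Both inputs are printed to one decimal. The smallest d that still rounds to them is about 1.35/2.05 = 0.659.

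- At d = 0.659, t power is 78.6% at 1% and 92.4% at 5%.
- At d = 1.35/2.02 = 0.668, t power is 80.0% at 1% and 93.1% at 5%.

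Rounding can therefore bring the 1% figure to 80%. Even at its limit it leaves the 5% figure above 92%.

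**Step 5. A different test?** A rank test at relative efficiency 0.864 (normal approximation, effective n = 54 × 0.864 = 46.7 per arm) gives 79.0% and 92.2%. That is close to the first figure but still not to the second. Adjusting for baseline, as the primary model does, would normally raise power and move further from both.

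**The case against.** The strongest defence is that 80% and 90% are conventional targets, and that 108 completers exceed both on the printed inputs. If the figures are read as floors, nothing promised is missed. This stands as far as consequences go: the trial is not underpowered on these inputs. It does not rescue the sentence, which presents the figures as calculated from the data, not as lower bounds.

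A second defence is rounding. It stands for the 1% figure and fails for the 5% figure (Step 4).

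Three stronger readings are tempting, and the documents do not support them.

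- **That 108 already contains an attrition allowance, so withdrawals are replaced twice over.** The arithmetic invites this, since 96/0.9 = 107. But the loss rate is chosen to fit, and the 90%-at-5% target would need a different one (86/0.8 = 107.5). The text also says the opposite: the 108 are completers, and "As we had not accounted for attrition if participants withdrew, these participants were replaced". The replacement rule is coherent as written, and the Abstract's minimum of 108 is compatible with it.
- **That the trial has two competing decision rules.** Quoting power at two levels is not specifying two tests. The article names no level for the primary comparison, but it is a condensed account, and the full protocol or analysis plan may settle the level.
- **That about 100 completers would do.** That number meets 80% at two-sided 1% on these inputs, but it gives no reason to cut the target when the effect estimate comes from a small trial.

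**Conclusion.** The power statement is wrong as written. On the printed difference, SD and 54 per arm, with a two-sided two-sample t-test, power is about 84% at 1% and 95% at 5%. The stated figures are too low by about 4 points at 1% (6 by normal approximation) and 5 points at 5%. The two figures are also mutually inconsistent: 80% at 1% goes with about 93% at 5%.

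The result assumes two-sided testing, which the article does not state, and an unadjusted comparison. A one-sided test, or the gain normally expected from baseline adjustment, would widen the gap. If the inputs are rounded, the 1% figure may be right and only the 5% figure is then unexplained.

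The error is conservative. It affects whether the calculation can be traced, not whether the sample is adequate, and it casts no doubt on the 108-completer target or on replacing withdrawals.

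**What to change.** Take one of two routes in the Sample size section.

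1. If the printed inputs are the ones used, restate along these lines: *108 completers (54 per arm) give about 84% power at the two-sided 1% level and about 95% at the two-sided 5% level to detect a difference of 1.4 stools per day with SD 2.0.*
2. If other inputs were used, disclose the difference, SD and test, and quote the powers they give at each level.

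On either route, say in the same sentence which significance level and sidedness the primary stool-frequency comparison uses, in agreement with the full protocol or analysis plan. Keep the target of 108 completers and the replacement rule unchanged.

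The cost is wording only: no extra participants and no change to design, conduct or analysis.

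### The 12-patient figure for mast cell numbers matches a one-group calculation and does not support 90% power for the planned mesalazine-versus-placebo comparison

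*Protocol article*

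**What the plan says.** The article lists two endpoints under Primary endpoint, one clinical and one mechanistic. The mechanistic one is "Difference in mast cell numbers per mm^2^ during weeks 11–12 of the treatment period".

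The second paragraph of Sample size says that far fewer patients than the 108 are needed for mast cell numbers and tryptase release. Its evidence is one published trial that "reported a 36% decrease in mast cell numbers from mean 9.2 (standard deviation 2.5"), "which would have required just 12 patients to show such a decrease with a power of 90% at the 1% significance level". It does not say which test was used, whether the test is one- or two-sided, or whether 12 is a total or a number per arm. It gives no mean, SD or effect for tryptase release.

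Trial design and Randomisation and blinding describe a two-arm, parallel, placebo-controlled trial with 1:1 allocation. Statistical analysis has mechanistic endpoints handled like the primary one, that is, by a general linear model with terms for baseline and treatment arm, after transformation where needed. Biopsies are taken at one centre, as the section heading shows: "Flexible Sigmoidoscopy and biopsies (Nottingham only". The number of participants to be biopsied there is not given.

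**The concern.** The published result is quoted as a fall from a starting mean, which is a before-and-after quantity. The trial's mechanistic endpoint is a difference between randomised arms. For the same mean difference and SD, a two-arm comparison needs about twice as many patients in each arm as a one-group test needs altogether, hence about four times the total by the normal formula. A figure of 12 for a standardised effect of about 1.3 at the 1% level therefore looked too small.

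This is the only sample-size justification for an endpoint placed under Primary endpoint, and reduction of mast cells is the trial's stated rationale. Because biopsies come from one centre, the 108 does not guarantee enough of them. A reader who takes 12 at face value would regard any biopsy subset above 12 as amply powered, when by unadjusted t-test at 1% any total below 38 falls short of 90%. A null mast cell result from a subset of that size could then be given more weight than it deserves.

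**Working it through.** **Inputs** (all from Sample size unless noted)

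- Mean 9.2, decrease 36%: δ = 0.36 × 9.2 = 3.312.
- SD 2.5, the only one given: d = 3.312 / 2.5 = 1.325.
- Power 90%, significance level 1%. Sidedness is not stated; two-sided is assumed.
- Two arms, 1:1 (Randomisation and blinding).

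**Step 1. Reproduce the 12.** For a one-group t-test with n patients, the noncentrality is d√n on n − 1 degrees of freedom.

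- n = 11: power 85.7%.
- n = 12: noncentrality 1.325 × √12 = 4.59, critical value 3.106 on 11 df, power 90.2%.

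The exact solution is n = 11.94, which rounds up to 12. Other one-group versions at 1% miss it: one-sided t gives 11, two-sided normal approximation 9, and one-sided normal approximation 8.

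**Step 2. Try to obtain 12 from two groups** at the 1% level with SD 2.5 in both arms.

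| Method | Per arm | Total |
|---|---|---|
| Two-sided t | 19 (18.69) | 38 |
| Two-sided normal: 2(2.576 + 1.282)² / 1.325² = 16.96 | 17 | 34 |
| One-sided t | 17 (16.27) | 34 |
| One-sided normal | 15 | 30 |

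None gives 12, in total or per arm.

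**Step 3. Power of the stated figure for a two-arm comparison.** The noncentrality is d√(n/2) on 2n − 2 df, with n per arm; two-sided 1%.

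| n per arm | Noncentrality | Critical t | Power (t) | Power (normal) |
|---|---|---|---|---|
| 6 (12 in total) | 2.29 | 3.169 | 25.8% | 38.9% |
| 12 (24 in total) | 3.25 | 2.819 | 66.4% | 74.8% |
| 18 (36 in total) | 3.97 | 2.728 | 88.5% | – |
| 19 (38 in total) | 4.08 | 2.719 | 90.6% | – |

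A one-sided t-test with 6 per arm gives 36.8%.

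**Step 4. Allow for the planned baseline adjustment.** With baseline correlation ρ the residual SD becomes 2.5√(1 − ρ²), and one further degree of freedom is lost. The article gives no ρ, so a range is shown (two-sided 1%).

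| ρ (assumed) | Power, 6 per arm | Power, 12 per arm |
|---|---|---|
| 0.3 | 27.5% | 71.1% |
| 0.5 | 34.4% | 80.8% |
| 0.7 | 52.0% | 94.5% |
| 0.8 | 70.4% | 99.2% |
| 0.85 | 83.0% | 99.9% |
| 0.9 | 95.2% | >99.9% |

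At ρ = 0.5, 90% needs 15 per arm (91.2%). With 6 per arm, 90% is first reached at a ρ of about 0.88.

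**Step 5. Allow for a log scale.** Assume the same coefficient of variation in both arms, 2.5 / 9.2 = 0.272. The log-scale SD is √ln(1 + 0.272²) = 0.267, the difference is −ln 0.64 = 0.446, and d = 1.672. Unadjusted t-test, two-sided 1%: 6 per arm 43.9%, 12 per arm 88.6%, 13 per arm 91.7%. With log scale and baseline adjustment together, 6 per arm gives 56.2% at ρ = 0.5 and 90.7% at ρ = 0.8.

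**The case against.** The strongest case on the other side has four parts.

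*The 12 is not a target.* The sentence is hypothetical and supports a remark that the mechanistic question needs far fewer patients than the clinical one. That remark survives, since 38 is still well below 108. A reader might infer that the biopsy sub-study itself has 26% power. The article does not support this. It sets no number or cap for biopsies, and the number taken at Nottingham may lie above or below 38. This part stands: the 26% is the power of the stated figure only.

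*The one-group origin is inferred.* This also stands. The match is close, but the test is not named. There are other routes to 12, read as a number per arm. A two-arm normal approximation at the two-sided 5% level gives 12 per arm, as does one at 1% if the SD is assumed to shrink in proportion to the mean. The first conflicts with "with a power of 90% at the 1% significance level"; the second adds an assumption that the article does not make.

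*The 12 might be per arm, and the planned model is not a raw t-test.* On a log scale 12 per arm gives 88.6%, and 91.5% with an assumed correlation of 0.3, which is close to the claim. But the text sets its number against 108, a total, so the total reading is the natural one. The rescue needs a per-arm reading and a transformation or a correlation, none of which is declared with the figure.

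*Thirty-eight is not the analysis-of-covariance requirement either.* Correct. It is the unadjusted raw-scale figure and should be labelled as such.

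Nor is this detail that an article may leave to a fuller document: the number is stated, and with its stated inputs it does not fit the planned comparison.

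**Conclusion.** The sentence is wrong as written for the comparison that the trial makes. With the stated inputs and the 1% level, 12 is reproduced only by a one-group two-sided t-test. For mesalazine versus placebo, by unadjusted two-sided t-test with SD 2.5 in both arms, it gives about 26% power if it is a total and about 66% if it is per arm. The unadjusted requirement is 38 in total (34 by normal approximation), about three times the stated figure on the total reading.

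The analysis allowed by the plan could lower that requirement: about 15 per arm at an assumed correlation of 0.5, or 13 per arm on the log scale with an assumed common coefficient of variation. Twelve in total reaches 90% only with a correlation near 0.88 on the raw scale, or near 0.8 combined with the log scale; the article states no correlation.

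The point should be fixed, but it is limited in reach. The total of 108 and the clinical primary analysis do not depend on it, and it does not show that the sub-study is underpowered.

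**What to change.** Replace the 12-patient statement in Sample size, in one of two ways:

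- Give a two-arm figure: 38 biopsied participants with evaluable mast cell counts (19 per arm) for 90% power at the two-sided 1% level, unadjusted, with SD 2.5 in each arm.
- Preferably, since it matches the planned model, state the between-arm power at the number of Nottingham participants expected to be biopsied, and declare any assumed baseline correlation or transformation.

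In either case say which test, which sidedness, and whether the number is a total or per arm. Remove tryptase release from the claim, or give the mean, SD and effect on which it rests.

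The cost is one sentence and a less favourable stated figure. The trial total does not change.
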